### Blinding

The trial will be single-blinded, where the embryologists involved in the embryo transfer procedure are blinded to group allocation, thus minimising performance bias. Measurement bias in unlikely to interfere with the trial analysis and result due to the objective nature of the primary outcome (live birth).

### Methods

The flow chart in figure 1 describes the participant flow through the trial. Women with a history of two to four IVF implantation failures, who fulfil the inclusion and exclusion criteria, are offered information about the Trophy trial, and invited to participate.

**Figure 1 F1:**
[figure not shown]
**Participants flow in the study**.

If the woman agrees to participate in the trial, further information and instructions relating to the trial are given [see Additional file 1], and she is requested to sign the trial consent form [see Additional file 2] by a clinician. Contact and baseline data are collected in the electronic Integrated Trial Management System (ITMS) [see Additional file 3]. Each woman will be randomised to either the intervention or the control group.

All women are given instructions to notify the clinic nurse by telephone at the start of their menstrual cycle to inform her of their intention to start treatment in that cycle. When the nurse receives the call from the woman, the nurse will randomise the patient, and if the woman is allocated to the OH group, will book an OH within 14 days of the beginning of menstruation. Women randomised to OH arm will attend the respective Unit for OH within 14 days of the beginning of menstruation. They will then be expected to start the IVF process according to a standard controlled ovarian stimulation protocol [24]. Women randomised to the control group will start the IVF process according to a standard controlled ovarian stimulation protocol without OH.

### Trial intervention

#### Outpatient hysteroscopy (OH)

The OH procedure will be performed in the first two weeks of the menstrual cycle by named surgeons in each of the participating centres (Box 1):

##### Box 1: Hysteroscopy Equipment

*Hysteroscope*

▪ Rigid hysteroscope (continuous flow; 30° forward-oblique view) assembled in an examination sheath with an atraumatic tip giving a total instrument outer diameter of up to 3.2 mm (often called "micro-hysteroscopy") [25]. The telescope can be used in a single- or double-flow mode with an operative channel for 5 French instruments for minor operative procedures, thus increasing the total instrument diameter up to 5.0 mm. The operative 5 French instruments are either mechanical (such as crocodile forceps, biopsy forceps and sharp and blunt scissors) or electrical (such as bipolar needle or coagulation probe)

*Distension media*

▪ An isotonic solution (0.9% Normal saline or Ringer lactate) administrated via a pressure-controlled pump or simple pressure cuff system is used. The pressure is preset at between 80-120 mmHg with the aim to use the lowest pressure required to distend the uterine cavity adequately.

*Pre-medication*

▪ No routine pre-operative analgesics, antibiotics, sedatives or cervical preparation is used. A pelvic ultrasound scan should be performed before the procedure is started. All women must have a negative pregnancy test prior to commencing the procedure.

*Procedure*

▪ Before the hysteroscopy is performed, the woman is fully counselled by the clinician and requested to sign a consent form.

▪ The woman is positioned in the dorso-lithotomy (semi-recumbent) position using comfortable leg rests.

▪ The perineum should be at the edge of the couch with the coccyx and sacrum well supported by the table.

▪ Either the 'touch' (Cuscoe's speculum) or 'no touch' (vaginoscopy) techniques is acceptable.

◦ Antiseptic preparation of the ectocervix is at the discretion of the operator (e.g. chlorhexidine)

▪ Entry into the uterine cavity is under direct vision using gentle manipulation to minimise trauma to the cervical canal.

◦ The use of minimal cervical dilatation is to be restricted to cases of cervical stenosis. A tenaculum can be applied to the anterior lip of the cervix to help straighten the cervical canal.

▪ Local cervical anaesthesia (direct cervical or para-cervical infiltration) using short acting local anaesthetic (lidocaine or mepivicaine) may be administered at the discretion of the operator to facilitate a minor degree of cervical dilatation and after obtaining the woman's consent.

▪ On entering the uterine cavity a systematic inspection should be conducted to include

◦ Panoramic inspection of the uterine cavity at the level of the uterine isthmus

◦ Inspection under higher magnification of the uterine cornua, tubal ostia, uterine fundus, lateral walls, anterior and posterior uterine walls.

◦ Information to be recorded must include (See Additional file 3):

▪ The appearance of the endometrium.

▪ Shape of the uterine cavity [regular vs. irregular contour; normal vs. enlarged vs. tubular (restricted) size]

▪ Presence and location of structural anomalies (polyps, fibroids, adhesions, congenital anomalies)

▪ The entire intra-cervical canal should be inspected whilst slowly withdrawing the hysteroscope.

▪ Uterine dimensions estimated and recorded to include

◦ Cervical canal length (cm)

▪ Cervical canal length should be obtained by visualising the internal cervical os, with the distal tip of the hysteroscope at this level and the operator's finger pressed against the shaft of the telescope to mark the level of the external cervical os.

◦ Uterine sound length (cm)

◦ Uterine cavity length [uterine sound length - cervical canal length (cm)]

◦ If uterine polyps, small submucous fibroids (≤ 0.5 cm diameter) or filmy adhesions are identified, simultaneous mechanical hysteroscopic treatment should be attempted and the feasibility and outcome of such procedures recorded.

*Post-procedure*

▪ Patients should be observed for a minimum period of 30 minutes in a sitting recovery area before being allowed to leave the clinic. Simple analgesics (e.g. paracetamol or diclofenac) may be administered if required.

Clear and accurate surgical data will be routinely collected on each patient recruited via a specific 'hysteroscopy findings chart' [see Additional file 3]. These data will be analysed for specific findings, and for rates of adverse events or treatment failures.

The first outcome assessment (pregnancy test) will be done approximately two weeks after egg collection. The second and third outcome assessments (clinical pregnancy and implantation) will be done via ultrasound scan performed between 6-7 weeks of gestation at the respective trial centres.

The primary outcome assessment (live birth beyond 24 weeks) is conducted after delivery to gather data on delivery outcomes. A member of the local research team will also check birth registers and in-patient records to track hospital admissions and pregnancy outcomes.

### Trial statistics

#### Number of participants

Sample size calculation was based on the observed IVF cycle outcome and differences in outcome from existing literature as well as on the judgement on what constitutes as a clinically Minimally Important Difference (MID). The MID was judged to be increasing the live birth rate per cycle started by 10% (from 25% to 35%). For this difference of 10% increase in the live birth rate, and for a power of over 80% and a double sided alpha error of 5%, 720 women in total will need to be recruited (360 in each arm of the trial). In order to allow for a "worst case scenario" dropout rate of 5%, we intend to recruit 758 women in total (379 in each arm of the trial). The base rate of 25% was based conservatively on the control arms of the studies included in the published systematic review [20] and the MID of 10% was defined following consultations with fertility practitioners. This difference is much smaller than has been suggested by existing literature [22], which has reported an overall 75% relative improvement in IVF cycle outcome. Hence, assuming a conservative actual absolute difference of 15% (25% to 40%) in live birth rate beyond 24 weeks, 758 participants will provide a power of 96% at a double sided alpha error of 1%. Based on a comprehensive audit data covering over 4,000 IVF cycles, approximately 40% of patients seen in participating centres will be eligible for inclusion in the study. Assuming a modest 50% recruitment rate, the target of 758 patients could be randomised in 24 months. This recruitment rate is realistic and easily achievable given that there are no similar trials ongoing in participating centres, and IVF patients are generally motivated to participate in research [26].

#### Statistical analysis

The analysis will be by intention to treat, and will be carried out in the following four steps:

##### Step 1: Summarising trial data

Baseline and outcome data will be summarised separately. For continuous variables, we will examine the distribution of the observations, and if normally distributed we will summarise them as means with standard deviations (SD). If they are non-normally distributed, then medians and inter-quartile ranges (IRQs) will be reported. Appropriate transformation will also be considered. For dichotomous data (e.g. pregnancy, implantation, clinical pregnancy and live birth), we will provide proportions (or percentages). In addition to baseline and outcome data, we will also summarise the recruitment numbers, those participants lost to follow-up, protocol violations and other relevant data. We will prepare a CONSORT flow diagram to display these results.

##### Step 2: Inter-group comparisons

The statistical procedures for comparisons will depend on the nature of the data: for example, for dichotomous outcomes, we will use Fisher's Exact Test or Chi-square as appropriate, and for continuous outcomes we will use t-test if the observations in each trial arm are normally distributed; if non-normally distributed, then Mann-Whitney-U test will be employed.

We appreciate that multitudes of comparisons can suffer from Type I (false-positive) error, and will therefore determine the success or failure of the study in terms of the single primary endpoint on which the power calculations are based: the live birth rate. Although p-values will be reported, the focus will be on providing 95% confidence intervals around point estimates as these are more useful in interpreting the findings of the trial.

##### Step 3: Sub-group analysis

We will give emphasis to analysis within planned (a priori) sub-groups (namely normal versus abnormal hysteroscopic findings). However, we are aware sub-group analysis is limited by statistical power and can suffer from false positive (due to multiplicity of comparisons) and false negative (due to reduced sample sizes) results, and will place limited importance on sub-group analysis findings in relation to the overall (global) findings. We will use post-hoc sub-group analysis only for the purpose of hypothesis generation.

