## Background

Only a third of in vitro fertilization (IVF) cycles started end in a pregnancy and one fourth result in a live birth [1,2]. Recurrent IVF implantation failure (two or more failed IVF cycles) is a very distressing experience to patients [3] and increases the financial burden on the couple or service provider. The aetiology of recurrent IVF implantation failure can be broadly attributed to embryonic or uterine factors, but remains unexplained in most cases [4]. A number of interventions have been proposed to improve IVF outcome in such women, but many of these interventions are not evidence-based [5,6]. As a result, there is considerable variation in the approach to investigations and management of recurrent IVF failure [7].

One of the common investigations proposed after recurrent IVF failure is outpatient hysteroscopy (OH). OH is a well-tolerated minimally-invasive procedure, which allows reliable visual assessment of the cervical canal and uterine cavity and provides the opportunity to perform therapy in the same setting [5,8-11]. Intra-uterine pathologies have been shown to be present in 25% of infertile patients [11]. Thus, routine OH prior to IVF has been suggested by a number of investigators to ensure normality of the uterine cavity before embryo transfer [12-19] although this proposition has not been tested in a randomised setting.

In order to capture all existing evidence on whether OH could improve the outcome of the subsequent IVF cycle in patients who have experienced recurrent IVF implantation failure, we conducted a systematic review and meta-analysis [20]. We identified two randomized studies [21,22] which examined the impact of OH on the outcome of the subsequent IVF cycle after two or more failed IVF attempts. Both studies included patients with normal uterine cavity on hysterosalpingography. The researchers in both studies performed the hysteroscopy as an outpatient procedure, used a 5-mm hysteroscope with a 30° view, reported no complications and discharged patients within one hour after the procedure. Both studies showed a statistically significant improvement in the clinical pregnancy rate in the group who had OH (pooled RR = 1.57, 95%CI 1.29-1.92, p < 0.00001). The number needed to treat with OH in order to achieve an additional clinical pregnancy in the study populations was 7 (95%CI 5-12). The miscarriage rate was not statistically different between the OH and control groups [20].

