### Exclusion criteria

Women who had less than two or more than four failed fresh IVF cycles ending in an embryo transfer, women aged 37 years or more at the time of randomisation, women who have had a hysteroscopy within 2 months of randomisation, the presence of submucous or intramural uterine fibroids distorting the uterine cavity or untreated tubal hydrosalpinges and a body mass index (BMI) above 35 (36 or higher).

The rationale for not including women aged 37 years and older is that the primary factor in IVF failure in this age group is related to embryo quality, which is unlikely to be corrected by uterine or endometrial manipulation. Submucous and intramural uterine fibroids distorting the uterine cavity and untreated tubal hydrosalpinges are known causes of IVF cycle failure and require specific treatment aimed at reversing their detrimental effects. Patients with a history of fibroids removal or treatment of tubal hydrosalpinges will not be excluded.

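### The only a priori subgroup, normal versus abnormal hysteroscopic findings, exists only in the OH arm after randomisation and so cannot estimate a treatment effect

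*Protocol article*

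**What the plan says.** Step 3 of the Statistical analysis section of the protocol article gives emphasis to "analysis within planned (a priori) sub-groups (namely normal versus abnormal hysteroscopic findings". No other a priori subgroup is named. The same step warns of low power and multiple comparisons, says that the authors "will place limited importance on sub-group analysis findings in relation to the overall (global) findings", and reserves post-hoc subgroups for hypothesis generation.

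The Methods text beside Figure 1 gives the order of events. When the woman telephones at the start of her cycle, "the nurse will randomise the patient, and if the woman is allocated to the OH group, will book an OH". For the other arm: "Women randomised to the control group will start the IVF process according to a standard controlled ovarian stimulation protocol without OH". Box 1 adds that if polyps, small submucous fibroids or filmy adhesions are found, "simultaneous mechanical hysteroscopic treatment should be attempted and the feasibility and outcome of such procedures recorded".

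**The concern.** A subgroup analysis of a treatment effect compares the randomised arms among women of the same type, so the type must be known, or knowable in the same way, in both arms. Here the type is revealed by the allocated procedure itself. It is known in one arm and never in the other.

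The subgroup is called a priori, is given emphasis and is set apart from post-hoc exploration, so a reader may well use it to judge who benefits from OH. The design cannot answer that question through this variable.

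**Working it through.** **Structure.** Four places in the protocol article, side by side:

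| Place | Content | Consequence |
|---|---|---|
| Methods, text at Figure 1 | Randomisation first; OH booked only if allocated | The finding is a post-randomisation variable |
| Same text | Controls start IVF without OH | No control can be classified |
| Exclusion criteria | Excludes "women who have had a hysteroscopy within 2 months of randomisation" | No recent pre-trial finding can stand in for controls |
| Box 1 | Certain lesions treated at the same procedure | The abnormal stratum mixes cavity prognosis with any effect of treating the lesion |

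Box 1 also says "Clear and accurate surgical data will be routinely collected on each patient recruited via a specific 'hysteroscopy findings chart". This does not fill the gap, because the chart records a procedure that controls do not have.

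Two kinds of contrast remain: normal versus abnormal within OH, or one OH stratum against the whole control arm. Neither is a randomised comparison.

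**The plan's own figures.** The plan gives no figure for the subgroup. Its sample size reproduces: 360 per arm gives 83.5% power for 25% versus 35% at two-sided 5%, consistent with the stated power of over 80%, and 720/0.95 = 758. The structural point does not depend on these.

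**Illustration of size.** Inputs:
- Live birth 25% overall: the control rate in Number of participants. It is applied to both arms, so OH is assumed to have no effect.
- Abnormal findings 25%: from the Background, "Intra-uterine pathologies have been shown to be present in 25% of infertile patients". That is infertile patients in general; its use here is an assumption.
- Live birth with abnormal findings, p_abn: not in the documents, so varied from 10% to 25%.
- 360 evaluable OH women: 0.25 × 360 = 90 abnormal and 270 normal.

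The rate with normal findings follows from p_norm = (0.25 − 0.25 × p_abn)/0.75. At p_abn = 0.15 this is (0.25 − 0.0375)/0.75 = 0.283.

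| p_abn | p_norm | Abnormal-OH minus all controls | Normal-OH minus all controls | Gap within OH (normal minus abnormal) |
|---|---|---|---|---|
| 10% | 30.0% | −15 points | +5.0 | 20 points |
| 15% | 28.3% | −10 | +3.3 | 13.3 |
| 20% | 26.7% | −5 | +1.7 | 6.7 |
| 25% | 25.0% | 0 | 0 | 0 |

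**Chance that the within-OH gap reaches p<0.05.** Step 2 names chi-square or Fisher's exact test, so the null standard error is pooled. At p_abn = 15% with 90 v 270:
- pooled SE = sqrt(0.25 × 0.75 × (1/90 + 1/270)) = 0.0527
- SE under the assumed rates = sqrt(0.15 × 0.85/90 + 0.283 × 0.717/270) = 0.0466
- (0.1333 − 1.96 × 0.0527)/0.0466 = 0.645, a probability of about 74%.

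Exact enumeration of the chi-square test gives 75%, and Fisher's test 73%. A z-test with unpooled variance would give 82%, but it is not a test the plan names. At p_abn = 20% the chi-square probability is about 23%, and at 25% it is the nominal 5%.

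**The case against.** **The misuse is inferred.** The protocol does not say that OH will be compared with control in each stratum, or that an interaction will be tested. Box 1 says that the hysteroscopy data will be analysed for findings, adverse events and treatment failures, so a descriptive intention is possible. This stands in part: a reader might infer that the plan commits to a biased OH-versus-control contrast, and the text does not go so far. But the analysis is presented as a subgroup analysis, with warnings about false positives and false negatives that belong to testing, and nothing marks it as descriptive.

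**The harm is limited.** Step 2 ties success or failure to live birth as the single primary endpoint, and Step 3 gives subgroups limited weight. This stands. A reader might infer that the trial's main conclusion is at risk; it is not. The caveat does not cure the defect, however, since its reasons are power and multiplicity. A larger sample would only make the non-randomised contrast look more certain.

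**The size is assumed.** This also stands. If findings do not predict live birth, the contrasts are unbiased. The 25% prevalence is for infertile patients generally, whereas this trial excludes cavity-distorting fibroids and untreated hydrosalpinges. Nor is the within-OH gap spurious, as a reader might infer: under the assumptions it is a real prognostic difference, misleading only if taken as an effect of OH.

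**New interaction subgroups are not needed.** Agreed. They are not required to correct the defect and would add the multiplicity that the plan tries to limit.

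**Conclusion.** The point holds as a defect in the specified subgroup. The protocol names one a priori subgroup, and its own design leaves that subgroup undefined in the control arm. This follows from the order of events alone and needs no numerical assumption.

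How far a reader could be misled does rest on assumptions. With no OH effect and the inputs above, the abnormal stratum set against all controls would differ by 5 to 15 points for p_abn from 20% down to 10%, and by nothing if findings are not prognostic. The 15% case gives a difference as large as the 10-point minimally important difference on which the trial is sized. The documents support the claim that the analysis could mislead if read as a treatment effect. They do not support the claim that it will mislead.

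**What to change.** In Step 3, remove normal versus abnormal findings as a treatment-effect subgroup. State instead that outcomes by hysteroscopic finding will be reported as a descriptive, non-randomised analysis within the OH arm only, with no inference about the effect of OH.

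If a subgroup for effect modification is wanted, define it by a variable recorded before randomisation in both arms and test it by a treatment-by-factor interaction. The minimisation factors in the Randomisation section (age, BMI, number of failed cycles, basal FSH) are already collected. This part is optional.

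The cost is wording only, with no new data and no change to the sample size or primary analysis. The plan gives up a claim about who benefits that it could not have supported.

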##### Step 4: Adjustments and sensitivity analyses

If randomisation fails to achieve balanced groups, then we will perform secondary analyses in which we will adjust for unbalanced prognostic factors using procedures such as logistic regression. If the primary unadjusted analysis and secondary adjusted analysis are at discordance, then we will give greater weighting to the primary analysis in the interpretation of trial findings. For issues such as losses to follow-up, missing data and protocol violations, we will attempt sensitivity analyses to explore the effect of these factors on the trial findings. As a secondary analysis, we will adjust for missing data using imputation techniques to explore the effects of such imputations on the trial findings.

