**Methods and design:**

Eligible and consenting women will be randomised to either OH or no OH using an internet based trial management programme that ensures allocation concealment and employs minimisation for important stratification variables including age, body mass index, basal follicle stimulating hormone level and number of previous failed IVF cycles. The primary outcome is live birth rate per IVF cycle started. Other outcomes include implantation, clinical pregnancy and miscarriage rates.

The sample size for this study has been estimated as 758 participants with 379 participants in each arm. Interim analysis will be conducted by an independent Data Monitoring Committee (DMC), and final analysis will be by intention to treat. A favourable ethical opinion has been obtained (REC reference: 09/H0804/32).

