### Randomisation

Third party, distant, internet-based randomisation will be used to ensure randomisation and allocation concealment. Participants will be randomised online via a secure internet facility in a 1:1 ratio through a third party independent Integrated Trial Management System (MedSciNet Clinical Trial Framework) that has been designed, developed and delivered according to ISI9001-2000 standards and compliant with FDA CFR21:11 requirements. A "minimisation" procedure using a computer-based algorithm will be used to avoid chance imbalances in important stratification variables, such as age, BMI, number of previous failed IVF cycles and basal FSH level (as dichotomous variables). The randomised allocation will not be given until all eligibility and stratification data have been given.

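### Allocation is minimised on four factors but the primary live birth test leaves them out, which is valid but conservative if they are prognostic; only the secondary analysis picks covariates by observed imbalance

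*Protocol article*

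**What the plan says.** The abstract of the protocol article says that the randomisation system "employs minimisation for important stratification variables including age, body mass index, basal follicle stimulating hormone level and number of previous failed IVF cycles". The Randomisation section confirms this, names the same four factors as dichotomous variables and sets a 1:1 ratio.

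Step 2 of the statistical analysis gives the test: "for dichotomous outcomes, we will use Fisher's Exact Test or Chi-square as appropriate". Live birth is such an outcome, and Step 2 will "determine the success or failure of the study in terms of the single primary endpoint on which the power calculations are based: the live birth". It also makes 95% confidence intervals, rather than p-values, the focus of reporting.

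Step 4 covers adjustment: "If randomisation fails to achieve balanced groups, then we will perform secondary analyses in which we will adjust for unbalanced prognostic factors". It mentions logistic regression as a possible method. It gives no criterion for imbalance and no list of covariates. It then ranks the two analyses: "If the primary unadjusted analysis and secondary adjusted analysis are at discordance, then we will give greater weighting to the primary analysis".

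These are stated choices. They are not details that a condensed article leaves to an analysis plan.

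**The concern.** Minimisation forces the arms to be alike on the four factors. The difference in live birth rates then varies less from trial to trial than under simple randomisation, provided that the factors predict live birth. A chi-square or Fisher test does not know this. Its standard error still contains the variation that the design has removed, so the test rejects less often than its nominal 5% under the null, the interval is wider than it need be, and some power is forgone.

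The imbalance trigger does not repair this. Factors used in the allocation will be balanced by construction, so the trigger passes over the very factors that the protocol calls important. What it can select is some other factor that happens to differ between the arms, and that selection is made after looking at the data. Prognostic value, fixed in advance, is the sounder ground for choosing covariates.

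**Working it through.** **1. The protocol's own figures.** Inputs from the section on number of participants: 25% against 35%, two-sided 5%, 360 per arm. With the pooled-variance test for two proportions,

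power = Φ{(0.10 − 1.96·√(2·0.30·0.70/360)) / √((0.25·0.75 + 0.35·0.65)/360)} = Φ{(0.10 − 0.0669)/0.03395} = 83.5%.

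Subtracting 1/360 from the numerator as a continuity correction gives 81.4%. Both agree with the stated power of over 80%. The dropout allowance also reproduces: 720/0.95 = 758.

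**2. Why the standard error is too large.** Let p be the overall risk and p_s the risk in covariate profile s. The unadjusted test uses a variance proportional to p(1 − p). When the arms are balanced on the profiles, the variance that applies is proportional to p(1 − p) − Var(p_s). The standard error is therefore too large by the factor

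k = 1/√(1 − Var(p_s)/[p(1 − p)]),

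and the actual two-sided error is 2·Φ(−1.96·k). If the factors are not prognostic, Var(p_s) = 0, k = 1 and nothing is lost. Minimisation balances each factor on its own rather than every profile, so k is an approximation and slightly high.

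**3. Assumptions, because the protocol gives none of these.** Four binary factors with prevalences 0.5, 0.3, 0.4 and 0.3; the same odds ratio for each; minimisation with a biased-coin probability of 0.8; 720 women; 40,000 simulated trials per scenario. The unadjusted chi-square test was compared with the Wald test for arm in a logistic model containing the four factors.

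| Odds ratio per factor | Var(p_s) at p = 0.25 | k | Type I error, unadjusted | Type I error, adjusted | Power, unadjusted | Power, adjusted | Power forgone (points) |
|---|---|---|---|---|---|---|---|
| 1.0 | 0 | 1.000 | 5.0% | 5.0% | 83.6% | 83.6% | 0 |
| 1.3 | 0.0021 | 1.006 | 4.9% | 5.1% | 83.8% | 84.2% | 0.4 |
| 1.5 | 0.0048 | 1.013 | 4.8% | 5.1% | 83.8% | 84.5% | 0.8 |
| 2.0 | 0.0130 | 1.036 | 4.3% | 5.0% | 84.3% | 86.3% | 2.0 |
| 2.5 | 0.0209 | 1.061 | 3.9% | 5.0% | 84.9% | 87.9% | 3.0 |

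The last column is taken from unrounded powers. The Monte Carlo standard error is about √(0.05·0.95/40,000) = 0.11 points for the error rates and √(0.84·0.16/40,000) = 0.18 points for power.

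**4. Consistency.** The formula in step 2 predicts errors of 4.9%, 4.7%, 4.2% and 3.8% for odds ratios of 1.3, 1.5, 2.0 and 2.5, each within about 0.1 points of the simulation. Working back from the simulated errors, the interval is too wide by about 0.3% (odds ratio 1.3: z = 1.966, and 1.966/1.960 = 1.003) to 5.5% (odds ratio 2.5: z = 2.067, and 2.067/1.960 = 1.055).

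**5. Would the trigger ever pick a minimised factor?** In the simulated trials the largest arm difference across the four factors averaged about 0.6 percentage points. Under simple randomisation, the standard deviation of the difference for one factor of prevalence 0.5 would be √(0.5·0.5·2/360) = 3.7 points. A factor held this closely would hardly ever be called unbalanced.

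**The case against.** The strongest defence is that nothing invalid is planned. The primary test is fixed in advance, errs only towards caution and delivers the power that the sample size section promises. All of that stands. A reader might infer that the trial is underpowered or that its error rate is inflated; the figures support neither.

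The size of the loss is also uncertain. Eligibility narrows the factors (age under 37, two to four failed cycles, an upper BMI limit) and the allocation dichotomises them, so the lower end of the range is quite possible. At an odds ratio of 2.5 for all four factors, the assumed live birth risk runs from about 3% to 52% across profiles, which nothing in the protocol supports. This limits the size of the point, not its direction.

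A reader might also infer that the primary analysis depends on the observed imbalance. It does not: it has no covariates, and success is judged on it. Only the secondary analysis has covariates chosen from the data. For the same reason the rule that favours the unadjusted result is not a separate fault. As the plan stands, it keeps a data-selected model from overriding a prespecified test, and it needs to change only if the primary analysis changes.

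The trigger is not empty either, since it covers any prognostic factor and not just the four. That is fair, but choosing covariates by chance imbalance remains a poor rule for those other factors too.

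Finally, the simulation tested dichotomised factors in a logistic model against chi-square. It did not evaluate Fisher's test, recorded values or a standardised risk difference. Centre is not named among the minimisation factors, so this argument gives no ground for requiring it.

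**Conclusion.** The point holds as a modest loss of efficiency and a weakness in the secondary analysis. To the extent that the four factors predict live birth, the primary test is valid but conservative: type I error of about 4.9% down to 3.9%, and about 0.4 to 3 points of power forgone, for assumed odds ratios of 1.3 to 2.5 per factor. If the factors are not prognostic, the loss is nil and adjustment cost no power in the simulation. The direction follows from the design. The size rests on assumed odds ratios, prevalences and biased-coin probability, and cannot be derived from the protocol. The trial still meets its planned power. The change is worth making because the intervals are to be the focus of reporting and the improvement needs no further recruitment.

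**What to change.** - Prespecify the primary analysis as a model of live birth on arm plus the four minimisation factors, at least as dichotomised for the allocation, or as recorded values where these are collected.
- Report a risk difference or risk ratio standardised from that model, with its 95% confidence interval. The odds ratio from an adjusted model is conditional on the covariates and does not answer the same question as the 25% to 35% comparison.
- Keep the unadjusted test as a supportive analysis.
- In Step 4, replace the imbalance trigger with this fixed covariate list, and amend the precedence rule so that the prespecified adjusted analysis is the primary one.
- Adding centre is optional and not part of this correction.

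The cost is a change of analysis wording, made before outcome data are seen by arm. The sample size stays as it is. The Randomisation section withholds the allocation until the stratification data have been entered, so the dichotomised covariates should be complete. That section does not show that the underlying values are held as well; if recorded values are to be used, this should be confirmed.
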